### Patient and Public Involvement

The OHP was tailored to long COVID with input from the long COVID clinic clinicians (2 occupational therapists). In addition, guidance was provided on the mode and timing of questionnaire administration with changes made to processes of administration to ensure participants will be prepared and supported. Mindful that the most common symptom of long COVID is fatigue and brain fog, and along with the overall focus of this study (ie, assessing the feasibility and acceptability of LC-OHP), patients with long COVID were not involved in refining the OHP at this stage. However, feedback from patients who used this program in previous studies has been implemented to make the program more succinct, colorful, and visual. Additionally, the delivery of the LC-OHP sessions will be arranged at patients’ convenience in terms of time and mode of delivery. Moreover, the views of patient participants who receive the program sessions will be collected by interviewing the pilot participants and the intervention participants at the end of the trial to further implement and adapt the program to people with long COVID. Finally, members of the public will form part of the trial DMC to monitor the progress of the study and contribute to the dissemination of its findings.

### Ethics Approval

This study received approval from the University of Suffolk Ethics committee (RETH21/004) and from the NHS Health Research Authority (IRAS 304234).

The study will be conducted in accordance with the Health Research Authority and the University of Suffolk guidelines on ethical conduct in research, as well as the approved study protocol.

### Dissemination Plan

The findings of this study will be communicated using different dissemination pathways. These include the use of academic pathways (ie, peer-reviewed journal articles and abstract submissions to local, national, and international conferences), social media pathways (ie, Twitter, YouTube, and LinkedIn), and sending summary findings to participants taking part in this study. The research team will work closely with the DMC, which will include members of the public to identify other appropriate pathways to disseminate the findings to the wider population.

## Results

This is an ongoing study, which began in November 2021. The outcomes will be feasibility and acceptability of the program (primary); and its efficacy on improving anxiety, depression, fatigue, self-efficacy, and quality of life (secondary). It is hypothesized that the LC-OHP will be acceptable by participants, will improve their health and psychosocial functioning, and will enable them to gain better understanding of this condition, increasing patient self-efficacy of their symptoms.

## Discussion

### Principal Findings

In moving this program forward, the feasibility and acceptability of the LC-OHP will be tested along with early measures as to its effectiveness. It is widely acknowledged that long COVID is a chronic condition that is associated with long term, multisystem manifestations. It is a serious health problem that has a significant impact on an individual’s physical, social, and psychological functioning. Though there is a good deal of uncertainty and much to be learned about long COVID, there is a pressing need for a specialized intervention to manage the condition.

While the LC-OHP has been used effectively for previous other chronic conditions [58-60,77], it has yet to be used for long COVID. This study has been designed to apply this program to people living with long COVID; however, there is no prior evidence to rely on at present as it is well recognized that COVID and long COVID are new conditions, and researchers and clinicians all over the world are still assessing how best these can be treated. Thus, the program in this study is going to be one of the first and innovative approaches to be used in order to provide additional support to this group of people.

The use of the OHP within this feasibility study offers a holistic approach that can provide a pathway for people to aid them through their recovery and to encourage them to be actively involved in their own management. It uses a person-centered approach and is in line with NICE guidelines and with the NHS plan 2021-22 for managing people with long COVID. It is therefore anticipated that an OHP specifically tailored to patients with long COVID will be acceptable by participants, will have a high retention rate, will improve their health and psychosocial functioning, and will enable them to gain better understanding of this condition, increasing self-management of their symptoms. This increase in self-management may reduce individuals’ contact with health or care services, reducing the demand on the NHS and care services seen during the pandemic. The impact of COVID-19 on mental health is widely acknowledged, and the LC-OHP could be a suitable approach to mitigate this impact and increase individuals’ empowerment and independence. Moreover, understanding participants’ views and perceptions on the LC-OHP is hoped to improve the program to provide better support for patients with long COVID.

### Strengths and Limitations

The study has some limitations. Due to the nature of the intervention, participants and researchers will not be blinded to group allocation; however, to avoid researcher-induced bias, randomization and interviews will be conducted independently.

To the authors’ best knowledge, this is the first study to examine an individualized holistic psychosocial program designed to address the needs of adults experiencing long COVID. The study is anticipated to provide evidence for the feasibility and acceptability of the used intervention in improving health outcomes for people experiencing long COVID. This feasibility trial uses a mixed methods design to assess procedural and methodological data in preparation for a fully powered large-scale trial.

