### Quantitative Data Collection

Following participation and baseline data collection, the research team will contact participants at 3-month intervals after randomization at a prearranged time to complete the questionnaires detailed in Table 1. At the end of the trial, participants in the intervention group will be asked to evaluate the LC-OHP by completing the Course Experience Questionnaire.

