### Qualitative Interviews

After the end of the trial, participants allocated to the intervention group will be invited to participate in a semistructured telephone interview conducted by an independent researcher (not the OHP facilitator). The interview will target exploring participants’ experience with the LC-OHP, identify their views on the program, and share any suggestions for improving the program for the future. Interviews will be audio-recorded and will be conducted at a time convenient to the participant. Interview duration will last up to 30 min (a max of 40 min if a participant requests more time) and will be guided by a topic guide developed by the research team. Participants will be interviewed until data saturation is reached. Textbox 1 shows a summary of the interview topic guide list.

Summary of the interview topic guide list.

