### Internal Pilot

The trial will start with an internal pilot, with the first 2 participants receiving a 1:1 session delivery. These participants will have a short interview (10 min) at the beginning of each session by the facilitator to identify their views about the previous session with respect to the program’s materials and to inform any necessary refinements before starting the program with other participants. The program will start 2 weeks following the internal pilot in order to give enough time for any modifications to be implemented. Figure 1 presents a flowchart of the trial process.

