### Participant Withdrawal

Participants can leave the study at any time without their care being compromised. All data collected from participants prior to withdrawal will be included in the analysis.

Participants’ withdrawals will be noted, and reasons will be classified under the following categories: (1) illness or death; (2) dropout or relocation; (3) loss of contact; and (4) failure to return the questionnaire.

Additionally, for the purpose of ensuring fidelity, the trial’s research team will interview a sample of participants who withdrew from the intervention to identify reasons behind their withdrawal, and to collect any suggestions that may improve the program for future participants. The withdrawing participants will be free to decline this interview without their usual care being affected.

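### Independent interviewing covers only the end-of-trial interviews, and people who leave early give no satisfaction score, so acceptability and satisfaction are at risk of overstatement

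*Protocol article*

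**What the plan says.** The Strengths and Limitations section concedes that neither participants nor researchers are blinded and offers one safeguard: "to avoid researcher-induced bias, randomization and interviews will be conducted independently". It names no exception.

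The Methods describe three kinds of interview.

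- **Qualitative Interviews** (end of trial): a "semistructured telephone interview conducted by an independent researcher (not the OHP facilitator"). Those asked are described by arm: "participants allocated to the intervention group will be invited to participate". The abstract caps the number at 20.
- **Internal Pilot**: "The trial will start with an internal pilot, with the first 2 participants receiving a 1:1 session delivery". They have a "short interview (10 min) at the beginning of each session by the facilitator to identify their views about the previous session". The stated use is to refine the programme before others start it.
- **Participant Withdrawal**: the trial's "research team will interview a sample of participants who withdrew from the intervention". They may decline.

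On satisfaction, Quantitative Data Collection says: "At the end of the trial, participants in the intervention group will be asked to evaluate the LC-OHP by completing the Course Experience Questionnaire". No earlier administration is described.

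The Participant Withdrawal section also sorts reasons into four groups: being ill or dying, dropping out or moving away, losing contact, and not returning a questionnaire. Primary Objectives lists acceptability (beside recruitment and retention) and satisfaction among the primary measures.

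**The concern.** In an open trial whose primary outcomes include participants' opinions, who asks and who is asked both matter. The article presents interviewer independence as a general protection, but its own Methods do not extend it to two of the three kinds of interview. A reader of the limitations section would credit the trial with more protection than it has.

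The second issue is separate: selection, not interviewer independence. The people most likely to be critical are those who stop. The satisfaction questionnaire comes too late for anyone who has left the study. The withdrawal interviews are the direct route to those people's reasons, but they cover only a sample. The four categories cannot stand in for the interviews, because none of them records that the programme was disliked, too burdensome or unsuitable.

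If favourable views are over-represented, the full-scale trial foreseen under Future Directions could be planned on an acceptability figure that is too high, with too little known about why people stop.

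**Working it through.** The document gives no figure to reproduce on this point. The check is a comparison of sections, followed by an illustrative size.

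**Step 1. The independence claim against each kind of interview**

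| Interview | Who asks | Who is asked | Claim met? |
|---|---|---|---|
| End of trial | Independent researcher, facilitator excluded | Those allocated to the intervention, up to 20 | Yes |
| Internal pilot | The facilitator, about the previous session | First 2 participants | No |
| Withdrawal | Research team, facilitator not excluded | A sample of those who withdraw from the intervention | Not stated to be |

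On the third row, the Intervention section has session recordings and the facilitator's checklist checked by a further member of the research team. This suggests that facilitators belong to that team. The section on withdrawal does not rule them out as interviewers.

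**Step 2. Who has a satisfaction score**

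The Course Experience Questionnaire is described only at the end of the trial. The rule that data collected before withdrawal stay in the analysis does not help, because someone who has left the study by then has no such score to keep. Someone who stops sessions but stays in the study can still be asked.

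**Step 3. Possible size of the overstatement**

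Let S be the proportion satisfied among those heard, d the proportion of the arm that stops and goes unheard, and g the amount by which satisfaction is lower among them.

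- Whole arm: (1 − d) × S + d × (S − g) = S − d × g
- Overstatement: S − (S − d × g) = d × g

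The document gives neither d nor g. Assumed ranges: d = 10% to 30% (3 to 9 of the 30 in the arm) and g = 20 or 50 percentage points.

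| d | g = 20 points | g = 50 points |
|---|---|---|
| 10% | 2 | 5 |
| 20% | 4 | 10 |
| 30% | 6 | 15 |

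The result is 2 to 15 points. It shrinks to the extent that those who stop are reached.

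**Step 4. Possible weight of the pilot interviews**

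Two people are 2/30 = 6.7% of the arm, or 2/20 = 10% of the end-of-trial interviewees if both are among them. Even if both gave falsely favourable views and these were counted, a simple proportion would move by at most about 7 to 10 points. Their influence on the content of the programme may be larger than that share. The Patient and Public Involvement section says that patients with long COVID had no part in refining the programme beforehand, so the pilot is the first such input described.

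**The case against.** The best reply is that the independence sentence naturally refers to the main experience interviews, which are independent, and that the rest is formative or supplementary. Pilot interviews are 10-minute checks with 2 people. No section says that pilot or withdrawal interviews determine acceptability. The term independent researcher is glossed only as someone other than the facilitator, so a research-team member could meet it; the withdrawal interviews are left open and do not flatly contradict the claim. Interviewing people who withdraw brings critical views in. Withdrawals and retention are reported whoever does the interviewing.

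Much of this stands. The clear contradiction is with the pilot interviews alone. The reply does not rescue an unqualified statement, and it does not supply a satisfaction score for those who have left.

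A reader might infer three stronger points that the document does not support.

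- **That acceptability is biased upward.** This is a risk. Nothing shows how views will be combined, and recruitment and retention rates do not depend on the interviewer.
- **That those who stop are mostly unheard, with a gap of about 21 points.** If 9 of 30 stop, with 20% satisfied against 90% of the other 21, the whole arm is (0.9 × 21 + 0.2 × 9)/30 = 69% against 90%. That is one assumed scenario in which no one who stops answers. The invitations to the interview and the questionnaire are framed by arm and not limited to completers.
- **That control participants must be interviewed because the appropriateness of the measures is a primary objective.** Completion and missing items in both arms also bear on this. Control interviews would take places from at most 20 meant to explore experience of the programme. That is a preference, not an error in the plan.

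**Conclusion.** The point holds in limited form. The independence statement is broader than the Methods: it is met by the end-of-trial interviews, contradicted by the facilitator-led pilot interviews, and not secured for the withdrawal interviews. Separately, a single end-of-trial satisfaction score, interviews with only a sample of those who withdraw, and categories that miss dissatisfaction and burden leave two primary measures open to selective loss of critical views.

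The 2 to 15 point range requires that those who stop are both less satisfied and unheard. With an arm of 30 and the assumed 3 to 9 people stopping, there is little reason to sample instead of inviting all. The changes are worth making because they are cheap and bear on primary outcomes.

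**What to change.** 1. **Reconcile the independence statement with the Methods.** Either limit it to the end-of-trial interviews and report pilot feedback separately as formative, or have the independent researcher already in the plan, not the facilitator, conduct the withdrawal interviews. On the second route the pilot still has to be named as an exception. The trial began in November 2021 and the pilot comes first, so for the pilot only wording and separate reporting may still be open.
2. **Invite everyone who withdraws from the intervention**, keeping their freedom to decline.
3. **Offer the Course Experience Questionnaire when a participant stops, as well as at the end of the trial.** Report satisfaction with all participants allocated to LC-OHP as the denominator, showing non-responders as their own group.

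The cost is protocol wording, a little more interviewer time for a handful of people, and possibly a less favourable satisfaction figure. No new staff role is needed.

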### Future Directions

The findings of this study will be used in implementing the suggestions given by participants in further adapting and tailoring the LC-OHP program to make it more suitable to people living with long COVID. The findings will also be used as pilot data to support conducting a fully powered large-scale randomized controlled trial to recruit a higher number of participants from multiple sites and from different geographical areas.

## Abbreviations

DMC: Data Management Committee
LC-OHP: Long COVID Optimal Health Program
NHS: National Health Service
NICE: National Institute for Health and Care Excellence
OHP: Optimal Health Program
SPIRIT: Standard Protocol Items: Recommendations for Interventional Trials
